## Abstract

Lithium is the first-line treatment for bipolar disorders and a first-line augmentation option for treatment-resistant unipolar depression. Due to its narrow therapeutic window and risk of toxicity, people taking lithium require regular blood testing to monitor lithium levels in the body. However, studies have reported that only half of lithium-treated patients receive adequate lithium monitoring. This protocol describes a trial that will test the feasibility and acceptability of a point-of-care (POC) lithium blood testing programme in patients with unipolar or bipolar affective disorders taking lithium as a maintenance treatment. The primary objectives are to establish whether testing the effectiveness of POC testing is feasible, by assessing recruitment, attrition, and adherence to monitoring guidelines compared to participants randomised to testing as usual; to test whether the programme is acceptable to patients; and to measure potential contamination bias. The secondary objectives are to examine changes in health-related quality of life, the use of healthcare services, and depressive and manic symptoms to inform the design of a larger multi-site randomised controlled trial (RCT). This feasibility RCT will recruit 80 participants with affective disorders who are taking lithium. Participants will be 1:1 randomised to either POC monitoring or monitoring as usual where they will be followed up at three research visits over 30 weeks. The proportion of patients meeting guidelines for lithium monitoring will be examined, alongside measures of acceptability, wellbeing, and health economic data. POC testing has the potential to significantly improve patient safety and satisfaction with lithium treatment.

## 1. Introduction

Lithium, a mood stabiliser, is the recommended first-line long-term pharmacological treatment for bipolar disorder (BD) [1] and is used as an augmentation treatment for those with unipolar depression who have not responded to an initial course of antidepressants [2]. Due to its narrow therapeutic window and risk of toxicity, people taking lithium require regular blood testing to monitor lithium levels throughout the course of treatment. The National Institute for Health and Care Excellence (NICE) recommends that lithium concentrations should range between 0.6 and 0.8 mmol/L for those who are being prescribed lithium for bipolar disorder for the first time or up to 1.0 mmol/L for those who have previously relapsed or continue to experience symptoms whilst receiving lithium [1]. Those with lithium levels below the therapeutic window may be at increased risk of relapse, whilst those with levels above the therapeutic window are at increased risk of side effects and lithium toxicity [3]. This is problematic as lithium levels are highly variable and are influenced by the timing of the lithium dose and factors such as food and water intake, exercise, and concomitant medications [4,5].

NICE guidelines recommend that lithium levels be monitored every 3 months in the first year of treatment and every 6 months thereafter, although high-risk groups (e.g., older adults, those taking drugs which interact with lithium, or people at risk of impaired renal or thyroid function) should continue to be monitored every 3 months [1]. Levels should also be measured 1 week after any dose changes. However, audit data from NHS services within the UK reported that only 30% of patients met monitoring guidelines for the frequency of lithium testing in 2009 [6]. Following a national quality improvement programme [7], this rose to 48% [8]; however, half of patients continued to receive inadequate lithium monitoring. A later study in one NHS trust reported that only 50.7% of patients were within the NICE-recommended therapeutic lithium range, meaning that many patients may not be receiving effective symptom relief or are at risk of more severe side effects [9]. Studies outside of the UK have reported similar findings [10,11]. Various procedural and individual-level factors may contribute to poor monitoring rates, including a lack of communication between services and differing practitioner roles.

Currently, lithium testing is undertaken via laboratory testing, which typically involves patients attending a service specifically to have venous blood drawn by a nurse or phlebotomist, and the test results are then added to a patient’s health record within a few days. However, a number of inefficiencies have been identified in this system, including the need to book a separate blood test, with the appointment often being scheduled weeks after being ordered by the doctor; patients having to call practices on busy phone lines for their test results; non-clinical staff communicating test results; and a lack of formal protocols for communicating results [12,13]. The perceived burden of blood testing has been reported to contribute to the declining rates of lithium prescribing worldwide [14,15].

This study aims to test the feasibility of a novel, point-of-care (POC) lithium blood testing programme to improve monitoring in people with unipolar and bipolar affective disorder. POC testing allows for lithium serum levels to be measured by members of the patient’s treatment team during an appointment using finger prick testing, giving results in minutes. POC testing has revolutionised other areas of healthcare, for example, glucose monitoring in diabetes [16]. Recently, POC testing was introduced to one NHS trust for clozapine monitoring in schizophrenia. The new system was found to be highly acceptable to patients and staff: 90% of patients felt that the system improved clinical care, and staff felt that the system allowed for faster changes to prescription, the identification of non-compliance, and ease of administration [17]. The initiative received two (of six) findings of outstanding practice from the Care Quality Commission Inspection [18] and is now used routinely within several NHS trusts. Introducing POC testing into psychiatry may help bring mental health monitoring in line with physical health practices, such as those used in diabetes management.

The primary objective of this study is to test the feasibility and acceptability of POC lithium blood testing compared to usual monitoring for patients with affective disorders (bipolar disorder and unipolar depression) receiving lithium maintenance treatment, in a randomised controlled trial (RCT) design. Feasibility will be assessed via participant recruitment and retention rates, lithium discontinuation rates, and adherence to monitoring guidelines. Contamination bias (e.g., crossover effects) will also be assessed. Acceptability will be assessed via clinician and patient questionnaires. The secondary objectives are to measure health-related outcomes, service utilisation, mood, adverse events, and side effects.

## 2. Methods

### 2.1. Design

The Lithium Point-of-Care testing (LiPOC) trial is a multi-site, two-arm, rater-blinded RCT investigating POC lithium testing versus testing as usual (TAU) over 30 weeks. A total of 80 participants will be recruited across four sites in London and one site in the North of England: South London and Maudsley NHS Foundation Trust (SLaM), West London NHS Trust (WLNHS), South West London & St George’s NHS Trust (SWLSTG), Central and North West London NHS Trust (CNWL), and Cumbria, Northumberland, Tyne and Wear NHS Foundation Trust (CNTW). Participants will be randomised 1:1 to POC or TAU. Participants will remain under the care of their treating clinicians, meaning that their lithium testing will take place within their usual services, regardless of allocation.

### 2.2. Participants

Participants will be recruited from any service within the five participating NHS trusts. They may be identified via (a) direct research team communications with clinicians; (b) adverts within trust premises; (c) searches of the clinical records of patients who have consented to be contacted for research, such as SLaM’s Consent for Contact and linked Clinical Records Interactive Search; and (d) existing databases of patients who, through other routes (such as previous study participation), have consented to be contacted by researchers within the Centre for Affective Disorders, King’s College London, or CNTW.

Inclusion criteria are as follows: (a) aged 18 and above, (b) a diagnosis of a unipolar or bipolar affective disorder, (c) due to have monitoring for lithium treatment at the beginning of this study and three monthly for the upcoming 6-month period, and (d) be receiving care at one of the participating trusts. Exclusion criteria are as follows: (a) a planned discontinuation of lithium treatment during the 30-week study period; (b) an affective disorder diagnosis for which lithium is not licenced (i.e., schizoaffective disorder); (c) clinically significant manic symptoms, defined as a Young Mania Rating Scale (YMRS) [19] score ≥ 20; and (d) inability to provide informed consent.

We will also invite clinicians to participate in an optional add-on study at the end of their patient’s participation in the trial to assess clinician experiences with the intervention. The only inclusion criterion is that the clinician must have been involved in the POC intervention of their patient who was enrolled in our trial.

### 2.3. Procedure

A study flowchart is shown in Figure 1. Participants will attend three visits: at week 0 (baseline), week 15, and week 30. All visits can take place remotely (i.e., via video call) or in person. Potential participants will first attend a screening visit to assess their eligibility and obtain verbal consent. Eligible participants will then be invited to attend a baseline visit, where written informed consent will be obtained, and demographic and baseline assessments will be administered (see Table 1). Following this, participants will be randomised, and the intervention will begin.

Follow-up visits will involve clinical and acceptability questionnaires, and any medication changes will be documented. In addition, researchers will obtain the levels of lithium, thyroid function test results, and serum levels of sodium, calcium, and creatinine via medical records. A timeline summarising patient visits during this study is shown in Figure 2.

### 2.4. Intervention

#### 2.4.1. POC Testing

Participants randomised to POC testing will have their lithium and creatinine serum levels tested with the Medimate device, a handheld tool which provides serum lithium and creatinine concentration from a finger prick blood sample within a few minutes. The device has been tested in line with international protocols, i.e., Clinical Laboratory Standards Institute Evaluation Protocols, which facilitate validation for manufacturers and laboratories in the US and EU. The device demonstrates an Allowable Total Error (ATE) rate for lithium levels below 10% or 0.1 mmol/L, exceeding both US CLIA regulations (maximum 20% or 0.3 mmol/L) and European consensus standards, and has a testing capacity of 0.2 mmol/L to 12 mmol/L [20]. It is also validated for measuring creatinine. Participants’ healthcare professionals will be asked to notify the study team when and where they are arranging the participants’ lithium test so that a study researcher can bring the testing device to administer the test to those in the POC arm. In this group, the Medimate device will be used for all lithium monitoring from randomisation up until week 30 of this study (provided agreement from clinicians and that they do not discontinue prior to this).

#### 2.4.2. TAU

Participants randomised to TAU will not receive any change to testing and will continue via laboratory testing as usual.

### 2.5. Randomisation and Blinding

Participants will be randomised 1:1 to POC or TAU within 24 h of completing the baseline assessment using King’s College Clinical Trials Unit independent web-based system. Randomisation will be stratified by site. The participant and healthcare professional will be notified of their allocation as soon as possible.

Participants and their clinicians will be aware of their treatment allocation. Researchers conducting the YMRS and Montgomery–Åsberg Depression Rating Scale (MADRS) outcome assessments will be blinded and will not have any other roles in the trial to maintain blinding. The trial statistician will also be blinded. The database will only refer to groups 01 and 02 without definition to maintain the blinding of the statistician.

### 2.6. Outcomes

Primary outcomes are as follows:Feasibility
Participant recruitment rates over the trial period.Participant retention and completion rates over 30 weeks.Rates of lithium discontinuation over 30 weeks.Adherence to lithium monitoring guidelines (proportion of participants meeting NICE guidelines for frequency testing and lithium levels within therapeutic range) over 30 weeks.
Patient acceptability
Patient monitoring acceptability questionnaires at week 15 and week 30.Patient preferences for POC testing versus laboratory testing.Perceived usefulness of POC monitoring.
Contamination bias
Monitoring rates between treatment-exposed versus non-exposed services.Changes in monitoring rates from first to last patients recruited.Participants’ monitoring rates from before trial (from electronic health records) versus during the trial.Clinician survey about service changes during the trial.

Secondary outcomes are as follows:Costs and economic outcomes
Health related-quality of life via the EuroQol-5D (EQ-5D) [21] at weeks 15 and 30.Service utilisation via the Client Service Receipt Inventory (CSRI) [22] at weeks 15 and 30.
Mood and affective symptoms
Manic symptoms via the YMRS at weeks 15 and 30 [19].Depression symptoms via the MADRS [23] at weeks 15 and 30.Depression, mania, and anxiety symptoms via the Maudsley visual analogue scales (M3VAS) [24] at weeks 15 and 30.
Side effects and adverse events
Lithium side-effects rating scale (LiSERS) [25] at weeks 15 and 30.Adverse events over 30 weeks.

### 2.7. Statistics

The sample size of 80 will enable the estimation of a 50% dropout rate with a confidence interval of ±10% [26].

Variables will be summarised using descriptive statistics (i.e., mean and standard deviation [SD] or median and interquartile range [IQR] or frequencies and proportions, as appropriate). Recruitment, retention, discontinuation, and measure completion rates will be described. The number and proportion of participants meeting NICE guidelines [1] for test frequency and therapeutic range compliance (usually 0.6 mmol/L–0.8 mmol/L but in certain specified circumstances either 0.8 mmol/L–1.0 mmol/L or 0.4–0.6 mmol/L) will be reported between study arms. Because our aim is to take three measurements per participant within the 30-week trial period, we are recruiting patients who require 3-monthly monitoring (with measurements at baseline/week 0, week 15, and week 30). However, due to the practical timing of clinic visits, some participants may only complete two measurements within this period; therefore two or three measurements will be considered adherent to monitoring guidelines, as long as they align with the participant’s scheduled monitoring timeframes. Acceptability questionnaires will be described quantitatively within subjects and between groups over time, as well as a qualitative analysis of narrative response questions.

The following will be analysed descriptively to investigate potential contamination bias (i.e., mean and SD or median and IQR or frequencies and proportions, as appropriate): (a) monitoring rates between treatment-exposed vs. non-exposed services, (b) changes in monitoring rates from the first to last patients recruited, (c) participants’ monitoring history from electronic health records, and (d) ratings from surveying clinicians about practice changes during the trial.

The unit costs of the intervention and use of other services will be estimated with the CSRI and compared between groups to identify the main cost impacts that should be measured in a future trial, in combination with health-related quality of life data from the EQ-5D to estimate quality-adjusted life years (QALYs). Generalised linear mixed models will estimate the between-arm differences at 15 and 30 weeks for the M3VAS, YMRS, MADRS, and LiSERS. These analyses will be used to estimate effect sizes for a future definitive RCT, as this feasibility RCT is not powered to detect treatment differences. The generalised linear mixed models will use all available data under a maximum likelihood framework. Missing follow-up data will not be imputed. Adverse events will be summarised descriptively between arms.

Analyses will be intention to treat (ITT). Sensitivity analyses may be carried out, excluding participants without clear information on their lithium treatment or monitoring.

Table 2 details key feasibility criteria to be met to proceed with a larger definitive RCT.

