**Figure 2 pharmaceuticals-18-01683-f002:**
[figure not shown]
Summary of patient visits and assessments. Blue indicates screening (pre-study), green indicates baseline and follow-up period.

**Table 1 pharmaceuticals-18-01683-t001:** Study procedures by visit.

Procedures/Measures	Screening (Pre-Study)	Baseline (W0)	Follow-Up 1 (W15)	Follow-Up 2 (W30)
Informed consent process	X	X		
Medical and psychiatric information	X	X		
Sociodemographic information	X	X		
Medication and lithium review	X	X	X	X
Randomisation		X		
EuroQol-5D (EQ-5D)		X	X	X
Client Service Receipt Inventory (CSRI)		X	X	X
Young Mania Rating Scale (YMRS)	X	X	X	X
Montgomery–Åsberg Depression Rating Scale (MADRS)		X	X	X
Maudsley visual analogue scales (M3VAS)		X	X	X
Lithium side-effects rating scale (LiSERS)		X	X	X
Patient monitoring acceptability questionnaire		X	X	X
Participant end of study feedback questions				X

**Table 2 pharmaceuticals-18-01683-t002:** Go–no-go criteria to be met to proceed with an efficacy trial.

	Go—Proceed with RCT	Amend—Proceed with Changes	Stop—Do Not Proceed Unless Changes Are Possible
Participant recruitment	80 in 12 months	80 reached but in >12 months	53 not reached by 12 months
POC monitoring acceptability	≥80% rating POC as “acceptable”	30–79% rating POC as “acceptable”	<30% rating POC as “acceptable”
Participant attrition rate	≤20% attrition	21–50% attrition	>50% attrition
Adherence to lithium monitoring guidelines	>60% adherence	30–60% adherence	<30% adherence

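### The sample-size sentence gives ±10% around a 50% dropout rate with no confidence level; at the conventional 95% level, 80 participants give about ±11 percentage points

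*Protocol article*

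**What the plan says.** The Abstract sets the size of the trial: "This feasibility RCT will recruit 80 participants with affective disorders who are taking lithium". Section 2.1 fixes equal allocation: "Participants will be randomised 1:1 to POC or TAU". Section 2.7 then gives the only rationale for that size: "The sample size of 80 will enable the estimation of a 50% dropout rate with a confidence interval of ±10" (the sentence goes on with a per cent sign and a citation). The sentence names one quantity, dropout, at one assumed value, 50%. It gives no confidence level and no interval method.

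Table 2 sets the criteria for going on to a definitive trial. For attrition the Go band is "≤20% attrition", and Stop applies above 50%. For acceptability the Go band is "≥80% rating POC as “acceptable". The bands are cut-offs for observed values. None refers to an interval, and none is labelled by arm.

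**The concern.** A precision statement can be checked from three inputs: the sample size, the assumed proportion and the confidence level. The article supplies the first two. With 95%, which most readers will assume when no level is given, the printed half-width does not come out.

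This matters because Section 2.7 offers no other basis for 80 participants, and the article says that the trial is not powered for treatment differences. The figure also describes precision at 50% attrition, which is the boundary between Amend and Stop in Table 2. A reader who relies on it will think the estimate there a little sharper than it will be.

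**Working it through.** **Inputs.** n = 80 (Abstract, Section 2.7); p = 0.50 and half-width 0.10 (Section 2.7); 1:1 allocation, so about 40 per arm (Section 2.1). The confidence level is not given: 95% two-sided is assumed and 90% is tried as the alternative. ±10% is read as percentage points. Read as a relative 10% of 50%, it would mean ±5 points, which is further from what 80 people give.

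**Attempt to reproduce ±10 at 95%.** The standard error is √(0.5 × 0.5 / 80) = 0.0559.

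- Wald: 1.96 × 0.0559 = 0.1096, so ±10.96 points (39.0% to 61.0%).
- Wilson: at p = 0.5 the half-width is z / (2√(n + z²)) = 1.96 / (2√83.84) = 0.107, so ±10.7.
- Jeffreys: 39.2% to 60.8%, so ±10.8.
- Exact (Clopper-Pearson): 38.6% to 61.4%, so ±11.4.
- Wald with continuity correction: 0.1096 + 0.5/80 = 0.1158, so ±11.6.

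All exceed 10, and all round to 11 or 12. The printed figure is not reproduced.

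**Sample size that ±10 points at 95% would need.**

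- Wald: 1.96² × 0.25 / 0.10² = 96.04, so 97.
- Wilson: 96.04 − 3.84 = 92.2, so 93.
- Exact: 104.
- Continuity-corrected: 106.

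**Level that would make ±10 correct at n = 80.** 0.10 / 0.0559 = 1.789, and 2Φ(1.789) − 1 = 0.926. By the Wald formula the figure corresponds to about 92.6% confidence.

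**Half-widths and sample sizes at 90%.**

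| Method | Half-width at n = 80 | n needed for ±10 |
|---|---|---|
| Wald | 9.2 | 68 |
| Wilson | 9.0 | 65 |
| Exact | 9.7 | 76 |
| Continuity-corrected | 9.8 | 78 |

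**Where the shortfall arises (95%, Wald, n = 80).**

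- At 20% attrition: 1.96 × √(0.2 × 0.8 / 80) = 0.088, so ±8.8.
- At 30%: ±10.04.
- At 50%: ±10.96.

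The stated ±10 is therefore met for dropout rates up to about 29% and missed by at most 1 point between there and 50%.

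**Side calculation for POC acceptability at the 80% Go threshold (95%).**

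- n = 40: 1.96 × √(0.16/40) = 0.124, so ±12.4 (Wilson 65% to 90%).
- n = 32, that is 40 less 20% attrition: 1.96 × √(0.16/32) = 0.139, so ±13.9 (Wilson 63% to 90%).

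**The case against.** The best defence is that 95% is the reader's assumption. The article states no level, it cites a source that is not available here, and every 90% interval lies within ±10. A 90% exact or continuity-corrected interval comes close to the printed value (±9.7 or ±9.8). This stands as a possible explanation but does not rescue the sentence. A reader would have to guess both an unstated level and a less usual method, and plain 90% Wald gives ±9.2. On either account the sentence needs the same repair.

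A second defence is that the discrepancy is small and changes no decision. That is right. Table 2 works on observed values, and at the 20% Go threshold the precision is better than stated.

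Two stronger readings are tempting, and the document supports neither. One is that the trial is too small and should enrol 97. Nothing in Table 2 depends on a half-width of exactly 10 points, so the arithmetic calls for a corrected statement and not for more participants. The other is that the ±10 is wrongly claimed for criteria that rest on one arm. The sentence claims precision for dropout only, and Table 2 assigns no criterion to an arm. Adherence is to be reported by arm under Section 2.7, but its progression criterion could be judged on all 80, where the half-width at 60% would be ±10.7 (it would be ±15.2 on 40).

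Only the rating of POC is single-arm by its nature. Even that is an inference, because Table 1 schedules the acceptability questionnaire without distinguishing arms. Omitting the precision of that criterion is not an error in the text.

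**Conclusion.** The point holds as a small arithmetic and reporting error in the sole sample-size rationale. With n = 80, p = 0.5 and 95% two-sided confidence, the half-width is about ±11 points (10.7 to 11.6 over the methods tried) against a stated ±10. The conclusion rests on taking ±10% as percentage points and 95% as the intended level. If another level was intended, the defect is that it was not stated. The practical effect on the attrition estimate is about 1 point at 50% and nil at the 20% Go threshold. It does not show that 80 participants are too few for a feasibility trial. The wider interval for POC acceptability, about ±12 to ±14 points at 80%, is useful context for reading Table 2 but is not part of the error.

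**What to change.** Replace the sentence in Section 2.7 with wording such as: *80 participants allow a 50% dropout rate to be estimated with a 95% confidence interval of ±11 percentage points (±8.8 at the 20% Go threshold).* If a different level or method lay behind the original figure, state both and give the half-width that they produce.

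Optionally, add that the POC acceptability proportion will in practice rest on the POC arm (about 40, fewer after attrition), with a 95% half-width of about ±12 to ±14 points at 80%, and report that proportion with its 95% interval.

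The cost is one sentence, or two with the optional addition, and a stated precision that is slightly less favourable. Enrolment, conduct and the Table 2 thresholds stay as they are.

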Because this is a feasibility trial, inferences about efficacy cannot be made from the results. A further limitation of this trial is that we are only including patients who require 3-monthly monitoring, therefore excluding a large proportion of patients on lithium maintenance treatment who require monitoring every 6 months. This decision was made in order to have an adequate number of scheduled monitoring appointments per participant within the time constraints of a feasibility trial. If this trial is successful, we would hope to also include those on 6-month monitoring in the larger confirmatory trial that would follow, which may include a longer follow-up period. A 12-month follow-up period would allow for the inclusion of patients who require 3-monthly or 6-monthly monitoring, with 4 or 2 expected monitoring appointments within the trial follow-up period, respectively. This would also allow longer-term adherence and efficacy to be assessed. However, a 12-month follow-up period presents challenges with regard to research investment. Finally, although the POC testing method provides lithium and creatinine serum levels, it does not provide monitoring of other parameters that the clinician may require or are recommended while taking lithium, such as urea and electrolytes, calcium, and thyroid function. NICE guidelines recommend that these parameters be monitored every 6 months or more frequently in certain circumstances [1].

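### Section 2.7 offers between-arm differences from about 80 participants as effect sizes for the definitive RCT, and they are too imprecise to set a target effect

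*Protocol article*

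**What the plan says.** Section 2.7 (Statistics) sets out the model-based comparison: "Generalised linear mixed models will estimate the between-arm differences at 15 and 30 weeks for the M3VAS, YMRS, MADRS, and LiSERS". It then states the purpose: "These analyses will be used to estimate effect sizes for a future definitive RCT". The reason given in that sentence is that the present trial lacks power for differences between arms.

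The same section justifies the sample size solely by how precisely a 50% dropout rate can be estimated. It says nothing about the precision of a difference between arms.

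The Discussion (section 3) lists as a limitation that "inferences about efficacy cannot be made from the results". The Abstract says that the secondary objectives, which include mood and quality of life, are meant to inform the design of the larger trial. Table 2 gives the criteria for proceeding: recruitment, acceptability of POC monitoring, attrition and adherence to monitoring guidelines.

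**The concern.** The sentence in section 2.7 states a use for the estimates, so this is not a detail left for another document. The reason it gives points the wrong way. A trial too small to detect a difference is also too small to estimate that difference well enough to plan on.

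If the observed difference became the target effect, a chance overestimate would produce an undersized definitive trial. A chance underestimate would produce an unnecessarily large one, or no usable calculation at all. Nothing in the text limits the models to the quantities a trial of this size can supply, and no minimum important difference or outside source for the target is named.

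**Working it through.** **Inputs from the protocol article**
- Total size (Abstract): "This feasibility RCT will recruit 80 participants with affective disorders who are taking lithium".
- Allocation (section 2.1): "Participants will be randomised 1:1 to POC or TAU", so 40 per arm.
- Attrition (Table 2): up to 20% for go, 21–50% for amend. If losses are balanced, 20% leaves 64 analysed (32 per arm) and 50% leaves 40 (20 per arm).

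**Assumptions not in the article:** two-sided 5% level; 90% power for the definitive trial (80% as a check); an observed standardised difference of 0.30 as illustration; baseline–follow-up correlation r of 0.6, with 0.5 and 0.7 as a range; equal attrition in the two arms.

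**1. The plan's own precision figure.** For p = 0.5 and n = 80, the half-width is z·√(0.25/80). This gives 0.110 at 95% and 0.092 at 90%. The stated ±10% is therefore close to, but not exactly, either one, and no confidence level is given. What matters here is that this is a one-sample proportion. It says nothing about a difference between arms.

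**2. Precision of a between-arm difference.** In SD units, SE = √(2/m · (1 − r²)) with m per arm, and the 95% half-width is 1.96 × SE.

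| m per arm | r = 0 | r = 0.5 | r = 0.7 |
|---|---|---|---|
| 40 (no attrition) | ±0.44 | ±0.38 | ±0.31 |
| 32 (20%) | ±0.49 | ±0.42 | ±0.35 |
| 20 (50%) | ±0.62 | ±0.54 | ±0.44 |

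At m = 32 and r = 0: √(2/32) = 0.25 and 1.96 × 0.25 = 0.49. At r = 0.6: 0.49 × √(1 − 0.36) = 0.49 × 0.8 = 0.39.

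The planned mixed model also uses week-15 data from people who later drop out, so its precision at week 30 may be a little better than the row for completers. The no-attrition row bounds that gain.

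**3. What an observed 0.30 would imply.** At 32 per arm, unadjusted, the CI is 0.30 ± 0.49, or −0.19 to 0.79. Adjusted at r = 0.6 it is 0.30 ± 0.39, or −0.09 to 0.69, which still includes zero.

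Size per arm of the definitive trial = 2(z₀.₉₇₅ + z_power)²/d², without baseline adjustment:
- 90% power: 2(1.960 + 1.282)²/0.30² gives 234; at d = 0.79 it gives 34; at d = −0.19 it is undefined.
- 80% power: 175 and 26; again undefined at the lower limit.

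**4. How often this would mislead.** Suppose the true difference is 0.30, with 32 per arm and no adjustment. The chance of an estimate at or below zero is Φ(−0.30/0.25) = Φ(−1.2) = 11.5%. In a simulation of 400,000 draws, the remaining estimates were used to size a trial at a nominal 80% power. The resulting n per arm had an interquartile range of about 65 to 413, against a correct value of 175. About 35% of those trials would have had true power below 50%. With a true difference of 0.5 and no attrition, the interquartile range was 37 to 124 (correct value 63), and 17% fell below 50% power.

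**5. What this trial can supply.** With 64 analysed (62 degrees of freedom), the 95% CI for an SD runs from about 0.85 to 1.21 times its estimate, which is usable for planning. The TAU adherence proportion is less precise: with 40 in the arm and p = 0.5, 1.96 × √(0.25/40) = ±15.5 percentage points. It should therefore be carried forward with its CI.

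**The case against.** The strongest reply is that the article never says the definitive trial will be sized on the observed difference. The word used is estimate. The four scales are secondary outcomes, and none is named as the next trial's primary outcome. The opening of the Discussion lists feasibility, acceptability and adherence, not mood, as what will inform the confirmatory trial. This stands in part: sizing is the natural reading of effect sizes for a future RCT, not an explicit plan. But the Abstract does give the secondary outcomes a role in that design, and section 2.7 does not say that the differences will not set the target.

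Baseline adjustment would also narrow the intervals. It would, but at 32 per arm and r = 0.7 the half-width is still ±0.35. Part of the remedy is already planned as well, since section 2.7 describes SDs, retention and adherence by arm.

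Four stronger readings are tempting, and the document does not support them:
- **That the Discussion contradicts section 2.7.** Estimating a difference is compatible with drawing no efficacy inference. The tension lies in carrying the estimate forward as a design effect.
- **That a near-zero estimate could end the programme.** No criterion in Table 2 involves mood or side effects.
- **That the estimates carry no information.** An interval of −0.19 to 0.79 still excludes differences above about 0.8 SD.
- **That the models omit baseline scores and site.** Section 2.5 says "Randomisation will be stratified by site", and section 2.7 names no covariates, but nothing excludes them. A condensed article commonly leaves such detail to the full protocol or SAP.

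**Conclusion.** The point holds for the one sentence on effect sizes. At the 20% attrition boundary, a standardised difference is known only to about ±0.49 SD unadjusted, or ±0.39 at an assumed correlation of 0.6. Across the scenarios tabulated, the half-width runs from 0.31 to 0.62 SD, as large as or larger than a difference of 0.30. An observed 0.30 is compatible with a definitive trial of 34 per arm at one end and with no calculable trial at the other. That is too imprecise to set a target effect.

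The finding rests on reading the sentence as concerning the target effect, and on the assumed effect sizes, correlations, power and balanced attrition. The conclusion is the same throughout the range tried. It concerns planning of the successor trial only. This trial's primary outcomes, the validity of its analyses and its progression decision are not affected.

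**What to change.** Replace the sentence on effect sizes in section 2.7 with wording such as:

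> Between-arm differences will be reported with 95% CIs for description only and will not set the target effect of the definitive RCT, which will be based on a minimum important difference; this trial will supply the outcome SD, baseline–follow-up correlation, TAU adherence proportion and retention, each with its CI.

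The cost is wording. No new data are needed, because the scales are collected at baseline and at weeks 15 and 30 (Table 1), and retention and adherence by arm are already to be reported. What is added is the CIs, the correlation, and a minimum important difference to be justified from outside this trial for whichever outcome the definitive RCT adopts. The only downside is that the trial no longer claims to supply an effect size.
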